#### Storage and distribution of trial treatments

A central pharmacy and distribution centre (Mawdsleys, Doncaster, UK) receives blinded interventions. On randomisation of a participant by the trial investigator/nurse, the pharmacy is notified of the container numbers of ointment and the device to be allocated to that participant via a web-based system. Trial treatments are then sent directly to the participant’s home following check and release by a qualified person.

#### Training in use of interventions

Before randomisation, all participants receive training in how to apply the ointment, including guidance on avoiding application to the eyelids and sensitive body sites such as the genital area. In addition, participants receive training in the correct use of the light therapy devices. A specially developed online training video is available (www.vitiligostudy.org.uk) and face-to-face training with the research nurse or investigator is given, covering how to record treatments, manage side effects and use of the treatment schedule. Written instructions are also provided for the participants to take home. Training takes place prior to randomisation and participants have the opportunity to ask questions and points of clarification. Anyone considered unable to follow the treatment regimen is excluded from the trial. Two weeks after randomisation, participants are telephoned by the trial team to check how they are getting on with the interventions and to confirm their understanding of treatment usage and completion of the treatment diaries. Additional training on use of either treatment is provided to the participants at this time point (over the telephone or face-to-face), if needed.

#### Choice of vitiligo patches for treatment

During the baseline clinic appointment, participants are asked to select up to three patches of vitiligo for treatment; one for each of three anatomical regions (head and neck, hands and feet and rest of body). One of these three patches is selected by the participants as being the patch that they would most like to see an improvement in. This will be used as the target patch for the primary outcome assessment. Vitiligo is known to respond differently at different body sites, with the face and neck being more likely to respond to treatment than the hands and feet.^20^ Training material provided to sites advised nurses to inform participants that patches on the hands and feet may be more difficult to treat so they may wish to choose a target patch from one of the other body regions.

If participants wish to treat additional patches of vitiligo they are free to do so, but the additional patches are not assessed as part of the trial. Participants are encouraged to consider the additional time burden of treating more than three patches, and to prioritise treatment of the study patches if the time burden becomes restrictive.

#### Adherence

Adherence is recorded in a treatment diary, which acts as an aide memoire to inform clinic appointment questions about the number of light treatment sessions and ointment applications undertaken since the last clinic visit. Collection of these data at each clinic visit (every 3 months) also helps the nurse to check participants’ understanding of treatment and to encourage adherence; additional training is provided at the clinic visit if it has been noticed the participant is not using the device appropriately or has misunderstood the treatment schedule.

#### Concomitant medications

Some medications can occasionally cause photosensitivity (a rash in areas of skin exposed to light), although the risk of these reactions is low for NB-UVB light. As such, no changes to existing medications are required at the onset of the trial.

At the end of the 9-month treatment phase, participants return their device and any unused ointment to the trial team and are asked not to use any active treatments for their vitiligo during the follow-up period (if possible), so that the duration of any observed treatment effect can be evaluated. If participants do start active vitiligo therapy, this is recorded in the 3-monthly questionnaires.

#### Treatment modification following adverse events

Participants are instructed to record adverse events in their treatment diaries and to contact their recruiting centre if they experience side effects of concern, or a serious adverse event (whether related to the trial treatment or not). For treatment-related side effects, or drug-induced photosensitivity, the site research team provide telephone advice or arrange for a dermatology consultation, as necessary. Treatment modifications, including reduction or suspension (temporary or permanent) of either topical corticosteroid or light therapy use is at the discretion of the trial nurse or dermatologist, as appropriate.

In case of a medical emergency where an active treatment of the ointment or the device would need to be stopped, active treatment of both interventions should be assumed. If knowledge of a participant’s allocation is necessary, the local investigator can access an online blind-break system held by NCTU, which is available 24 hours a day.

### Outcomes

Previous research has demonstrated a discrepancy between what is collected in vitiligo trials and the outcomes that patients feel are most important to them.^21^ An international e-Delphi consensus exercise^22^ established core outcome domains for vitiligo trials, including: repigmentation, cosmetic acceptability of treatment response, maintenance of gained repigmentation, cessation of spread, quality of life, burden of treatment and safety. The HI-Light Vitiligo Trial will assess all of these core outcome domains.

#### Primary outcome

The primary outcome of treatment success will be assessed at 9 months for a target patch of vitiligo for each participant: defined as the patch that the participant would most like to see an improvement in. Treatment success is defined as a participant’s report that their vitiligo is either ‘a lot less noticeable’ or ‘no longer noticeable’ in response to the question: ‘Compared with the start of the study, how noticeable is the vitiligo now?' using the validated Vitiligo Noticeability Scale (VNS).^23^ Participants are shown a digital image of their vitiligo at baseline to inform this judgement at 9 months. Preliminary validation of the VNS has shown it to have good face validity with patients and good construct validity, acceptability and interpretability.^23^

Digital images of the target patch (taken at baseline and 9 months) will be assessed by a panel of independent assessors comprising three patients with vitiligo, thus providing blinded assessment of the primary outcome to explore the impact of detection bias, due to potential unblinding of the trial participants, in sensitivity analysis.

#### Secondary outcomes during treatment phase

*Onset of treatment response:* assessed by participant and investigator for each patch of vitiligo in each of the three body regions. The question ‘Compared with the start of the study, has there been a change in the vitiligo patch?’ is asked at 3, 6 and 9 months, with the patient and investigator responding with one of the following: stayed the same, improved, got worse.
*Percentage repigmentation*: recorded by investigators at 3, 6 and 9 months clinic visits for each of the assessed patches. In addition, an independent dermatologist will provide blinded assessment based on photos of the target patch at baseline and 9 months.Pattern of repigmentation (perifollicular, marginal, diffuse, mixed, hyperpigmentation) will be recorded for descriptive purposes.
*Quality of life:* assessed at three time points: baseline, end of treatment (9 months) and end of follow-up (21 months). VitiQOL (vitiligo-specific), Skindex 29 (dermatology-specific) and EQ-5D-5L (generic health-related quality of life) are completed by adults aged 18 years and above.^24–28^ All children up to and including 17 years of age at randomisation will complete the CHU 9D (children’s health-related quality of life), and children aged 11 years and above at randomisation will complete the EQ-5D-5L (generic health-related quality of life).^28–31^

*Time burden of treatment*: participant-reported treatment burden at 3, 6 and 9 months based on average duration and number of treatment sessions and adherence with the treatment schedule. To be presented for light therapy and topical corticosteroid therapy separately.

#### Secondary outcome during treatment and follow-up phase

*Participant-reported treatment success, analysed by body region:* using the VNS, assessed for each patch at 3, 6 and 9 months, and again in follow-up questionnaires at 12, 15, 18 and 21 months, to assess long-term patient-reported noticeability for each body region.
*Resource use to inform within-trial cost-effectiveness analysis from an NHS perspective (primary) and a family perspective (secondary).* Participant self-report of healthcare appointments (number, which professional, and if related to vitiligo), prescriptions and personal expenses, in relation to vitiligo over the course of the treatment and follow-up phases.

#### Secondary outcome during follow-up phase only

*Maintenance of treatment response*: assessed by participants for each patch of vitiligo in each of the three body regions during the long-term follow-up period (12, 15, 18 and 21 months questionnaires). The question asked is “Thinking now about since you stopped using the study treatments, has the vitiligo on your [*Head and Neck, Hands and Feet, Rest of Body*] patch: stayed the same, improved, got worse?” Since this response is a subjective personal assessment of how the treatment response is perceived, participants are not shown their end of treatment photograph when making this judgement.

#### Safety outcomes

The safety end points are proportion of adverse device effects and adverse reactions to the topical corticosteroid and NB-UVB during the treatment phase.

Adverse events are recorded in the trial database, and monitored by the trial coordinating centre and relevant oversight committees. Erythema (redness) of grade 1 or 2 is not considered an adverse event as this is an expected treatment response from use of NB-UVB. All serious adverse events (SAEs) are reported directly to the trial coordinating centre and assessed for seriousness, expectedness and causality by the Chief Investigator, or delegated medical monitor. SAEs are recorded and reported to the Medicines Health Regulatory Authority (MHRA) and Research Ethics Committee (REC) as part of the annual reports. Serious unsuspected serious adverse reaction (SUSARs) will be reported within the statutory timeframes to the MHRA and REC.

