### Objectives

Primary objective:To evaluate the comparative safety and effectiveness of home-based interventions (potent topical corticosteroids and hand-held NB-UVB light) for the management of early and limited vitiligo in adults and children. Specifically, we are comparing:Potent topical corticosteroid (mometasone furoate 0.1% ointment) with hand-held NB-UVB light;Potent topical corticosteroid (mometasone furoate 0.1% ointment) with combination of hand-held NB-UVB light and potent topical corticosteroid.

Secondary objectives:To assess whether treatment response (if any) is maintained once the intervention is stopped.To compare the cost-effectiveness of the interventions from a National Health Service (NHS) and a family perspective.

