While every effort is made to maintain blinding of the trial interventions, there is a risk that participants may be able to guess their treatment allocation as a result of side effects of the interventions (eg, redness and tanning of the skin). To minimise detection bias, outcomes will be assessed by blinded assessors (both independent clinicians and a panel of patients), using digital images taken at baseline and at 9 months. Participant information leaflets will emphasise that all participants will receive at least one active treatment for their vitiligo, thus reducing potential unblinding due to lack of treatment response. During our previous trial in which participants were randomised to active or dummy light therapy devices, 70% (19/27) of participants and 40% (16/27) of research nurses, guessed treatment allocation correctly. The main reasons for unblinding of the research nurses were redness of the skin (30% (3/10)) and improvement in vitiligo (60% (6/10)) in the active group, and lack of treatment response (100% (6/6)) in the placebo group.

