### Interventions

#### Topical therapy: potent topical corticosteroid

Mometasone furoate 0.1% ointment (Elocon, Merck, Sharp and Dohme, PL00025/0578), a potent corticosteroid used once daily, has been recommended in the European Clinical Guidelines for the management of vitiligo.^9^ In order to minimise the risk of adverse reactions, the Guidelines recommend a discontinuous regimen involving periods of use followed by break periods. Possible adverse reactions to mometasone furoate 0.1% (as listed in the Summary of Product Characteristics^18^) include: infection, folliculitis, paraesthesia, burning sensation, contact dermatitis, skin hypopigmentation, hypertrichosis, skin striae, acneiform dermatitis, skin atrophy, pruritus, application site pain and visual disturbance. Participants are advised to stop treatment with the ointment if they notice any side effects and to contact the local research team for review and advice on when to restart treatment.

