#### Light therapy: NB-UVB device

Several brands of hand-held NB-UVB units are CE marked for use in treating vitiligo and suitable for use at home. Dermfix 1000 MX units are being used for this trial.

Known adverse reactions to NB-UVB light include: erythema, blistering, burns, pruritus, perilesional hyperpigmentation, hypersensitivity reactions, cold sores and dry skin. Potential long-term risks include skin ageing and increased risk of skin cancer. Side effects can be reduced by appropriate use of the device.

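### The safety endpoint counts only events attributed to a trial product, so the between-arm comparison of harm is open to attribution bias

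*Protocol article*

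**What the plan says.** The Objectives section of the protocol article makes safety a comparative question within the primary objective: "To evaluate the comparative safety and effectiveness of home-based interventions". The Safety outcomes section then fixes what is measured over the treatment phase: "The safety end points are proportion of adverse device effects and adverse reactions to the topical corticosteroid and NB-UVB". In Table 1 the scheduled safety item is likewise adverse reactions.

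Data capture appears wider than the endpoint. Under Treatment modification following adverse events, "Participants are instructed to record adverse events in their treatment diaries". Under Safety outcomes, "Adverse events are recorded in the trial database, and monitored by the trial coordinating centre and relevant oversight committees". Causality assessment is described only for serious adverse events, and is given to the Chief Investigator or a delegated medical monitor.

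On blinding, the Randomisation and blinding section lists participants, nurses and principal investigators as blinded, but concedes that "there is a risk that participants may be able to guess their treatment allocation as a result of side effects of the interventions". The strengths and limitations list adds that this applies particularly with active light.

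**The concern.** An adverse reaction or an adverse device effect is an event plus a verdict on its cause. Randomisation makes the arms comparable for events. It does not make them comparable for verdicts, which can depend on what the person deciding believes the participant received.

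Three features of this trial make the verdict fragile. First, every participant uses both an ointment and a device on the treated patches, and either may be inactive. Second, the listed reactions overlap. The ointment list ends with "skin atrophy, pruritus, application site pain and visual disturbance" and also names a burning sensation; the device list reads "erythema, blistering, burns, pruritus, perilesional hyperpigmentation, hypersensitivity reactions, cold sores and dry skin". Third, the article describes the dummy device as having no known side effects and the vehicle as nearly free of them, so anyone who believes a product is inactive has a reason not to charge an event to it. The signs expected to give allocation away are of the same kind as the events to be attributed.

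At stake is the safety half of the primary objective: a true difference in harm could be understated, or an apparent one could arise from how events were attributed.

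**Working it through.** **Figures in the article.** It gives no adverse-event rate and no power for safety. The only relevant figures are correct guesses of allocation in the previous trial (Randomisation and blinding):

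- Participants: 19/27 = 70.4%, which reproduces the printed 70% (exact 95% CI 49.8% to 86.2%).
- Nurses: 16/27 = 59.3% (38.8% to 77.6%), against a printed 40%. The reasons for unblinding use denominators of 10 and 6, which sum to 16 and support the count. This mismatch is a separate error, and nothing below relies on it.

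**Model.** Let r be the risk of a relevant event in an arm and a the probability that an event is attributed to a product. The stated endpoint then estimates r × a. A count of all recorded events estimates r.

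**Case 1: attribution incomplete but equal across arms.** With assumed true risks of 10% and 20%:

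| a | Observed | Risk difference | Risk ratio |
|---|---|---|---|
| 1.0 | 10% v 20% | 10 points | 2 |
| 0.8 | 8% v 16% | 8 points | 2 |
| 0.5 | 5% v 10% | 5 points | 2 |

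The risk difference shrinks in proportion to a, the risk ratio does not change, and no false difference appears.

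**Case 2: attribution differs by arm, true risks equal.** With an assumed r = 20% in both arms and 516/3 = 172 per arm (two-sided 5% test):

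| a in the two arms | Observed | False difference | Risk ratio | Chance of p < 0.05 |
|---|---|---|---|---|
| 50% v 50% | 10% v 10% | 0 | 1.0 | 5% |
| 50% v 60% | 10% v 12% | 2 points | 1.2 | about 9% |
| 40% v 60% | 8% v 12% | 4 points | 1.5 | about 23% |
| 30% v 70% | 6% v 14% | 8 points | 2.33 | about 70% |

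With r varied from 10% to 40%, the false difference over the unequal rows runs from 0.10 × (0.60 − 0.50) = 1 point to 0.40 × (0.70 − 0.30) = 16 points.

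**All recorded events.** Because a drops out, the expected difference is 10 points in Case 1 and 0 in every row of Case 2, provided that events are recorded equally in all arms.

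The values of r and a are assumptions chosen to show a range. None comes from the article.

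**The case against.** The article names no assessor for non-serious events. Participants are asked to record events, not to decide their cause, and site staff are formally blinded. The full protocol, which the article says is available, may set out who attributes and how, so silence on this in a condensed article is no finding. The dummy device, the vehicle and central causality assessment of serious events protect safety data too, and an independent committee sees unblinded data. Arms can be compared on any attributed event without splitting events by product. Restricting to attributed events also removes unrelated background events. All of this stands. It limits the point to the endpoint as stated, and to a risk of bias.

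A reader might go further and infer that the comparison is biased against light, using the participants' guess rate. Suppose that 20% in each arm have a light-type event, attributed to the device 90% of the time if the light is believed active and 50% if it is believed dummy. With 70% correct guesses, attribution is 0.7 × 0.9 + 0.3 × 0.5 = 78% with active light and 0.3 × 0.9 + 0.7 × 0.5 = 62% with dummy, so 15.6% against 12.4%. The article does not support this inference, for three reasons:

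- It never makes participants the people who attribute. With the nurses' printed 40%, the same formula gives 66% and 74%, so 13.2% against 14.8%, and the direction reverses. With 16/27 it gives 14.7% against 13.3%, about 1.5 points.
- It treats the guess as independent of the event, whereas the article says that guesses arise from side effects. If an event itself prompts the belief that the light is active, people with events in both arms tend to share that belief and the gap shrinks towards zero.
- The previous trial compared active with dummy light. Here everyone receives at least one active treatment, which the article expects to reduce unblinding from lack of response.

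**Conclusion.** The point holds as a weakness of the stated endpoint. A comparison that belongs to the primary objective rests on causal attribution, which randomisation does not protect, in a trial where each participant uses two products with overlapping listed reactions and side effects are expected to reveal allocation to some participants.

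The effect is a dilution of the risk difference if attribution is incomplete and equal across arms, and a false difference only if attribution varies by arm. The second is plausible but not shown. Neither its size nor its direction can be computed from the article; the 1 to 16 points rest wholly on assumed values. The article also does not support saying that attribution is made by unblinded people. It expects guessing by participants, and it does not identify who attributes non-serious events.

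**What to change.** Make the main between-arm safety comparison the proportion of participants with any recorded adverse event during the treatment phase, by randomised arm and whatever the attributed cause. Show skin events on treated areas separately if event location is recorded, which the article does not state. Keep attributed adverse reactions and device effects as supportive description.

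Before adopting this, confirm that events thought unrelated to treatment are also entered. Table 1 lists only adverse reactions, while the Safety outcomes and Treatment modification sections say that adverse events are recorded. If unrelated events are not entered, the new comparison would inherit the same filter.

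If they are entered, the cost is a change of endpoint wording and one additional table, with no change to visits or sample size. There are two downsides. Background events add noise, which the treated-area table would limit. Self-report by participants who guess their allocation remains a limitation, because removing the attribution step does not remove differences in what people choose to report. Erythema of grade 1 or 2, which the article does not class as an adverse event, would still fall outside the count; that is a separate matter.

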5	What is the ideal practice for dose adjustment following symptomatic erythema?	HI-Light Trial: patient self-adjustment for grades 1 and 2 erythema (according to flow chart in patient handbook) and investigator adjusted dosing for grades 3 and 4. Rationale: the upwards and downwards dosing used in the trial reflects the clinical practice of most UK phototherapy services.
6	How should the protocol be adjusted for missed doses?	HI-Light Trial: varies in function of number of missed treatments. 1 or 2 missed: go back one step on treatment schedule; 3 missed: go back two steps on treatment schedule; 4–6 missed: 50% of last dose; 6+ missed restart treatment schedule from beginning. Rationale: this conservative approach ensures that participants who have missed a lot of doses are not at risk of symptomatic erythema when they restart treatment.
7	How should a ‘course’ of NB-UVB therapy be defined? (ie, At what interval should further exposure be reassessed?)	*Not directly applicable within the scope of the trial.*
8	What is the maximum number of exposures allowable for patients with vitiligo given the potential risk of carcinogenesis with NB-UVB?	*Not directly applicable within the scope of the trial.* Participants in the trial will only be treating limited areas of skin and the total number of treatments will be less than the current maximum recommended number of treatments.
9	Should dosing strategies differ when treating children with vitiligo?	HI-Light Trial: children are treated in the same way as adults. Parents are given the choice of what patches they are comfortable treating, and may opt out of treating sensitive areas if they wish to do so. Rationale: the home-based treatment is more flexible than hospital-based full-body treatment, so it is possible for children to be treated in the same way as adults.
10	Should shielding of sensitive structures (eyelids, areolas and genitals) be a universal requirement, or is it safe to expose these areas if affected by vitiligo?	HI-Light Trial: the trial excludes treatment of vitiligo in the genital region. Other sensitive areas can be treated if they are affected by vitiligo, but will not otherwise be exposed to NB-UVB due to the localised nature of treatment using a hand-held device. If treating the eyes, patients are advised to seek assistance from someone else so that they can keep their eyes closed during treatment, thus reducing the risk of accidental exposure during treatment.

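### Grade 1–2 erythema is kept out of adverse events, and so apparently out of the safety endpoint, although the protocol lists erythema of any grade as a reaction to NB-UVB

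*Protocol article*

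**What the plan says.** The Objectives section gives safety equal standing with effectiveness in the primary objective: "To evaluate the comparative safety and effectiveness of home-based interventions".

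The Safety outcomes section then defines what is counted: "The safety end points are proportion of adverse device effects and adverse reactions to the topical corticosteroid and NB-UVB during the treatment phase". In the next paragraph it sets the exception: "Erythema (redness) of grade 1 or 2 is not considered an adverse event as this is an expected treatment response from use of NB-UVB". It names no similar exception for any expected corticosteroid reaction.

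The section on the NB-UVB device describes the same reaction differently: "Known adverse reactions to NB-UVB light include: erythema, blistering, burns, pruritus, perilesional hyperpigmentation, hypersensitivity reactions, cold sores and dry skin". Erythema appears there with no grade threshold.

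Table 2, question 5, shows that the trial works with a four-grade scale: "patient self-adjustment for grades 1 and 2 erythema (according to flow chart in patient handbook) and investigator adjusted dosing for grades 3 and 4".

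Table 3 (Protocol amendments) dates the erythema rule to version 3.0, 30 September 2015. Trial status puts the first randomisation in July 2015.

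**The concern.** One section treats erythema as an adverse reaction to light. Another says that its two lower grades are not adverse events. The endpoint is built from adverse reactions and device effects, so its content depends on which section governs. That a reaction is expected bears on how it is reported to regulators. It does not by itself settle whether the reaction belongs in a comparison of tolerability between arms.

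The rule also does not fall evenly. It can remove few events from the corticosteroid-plus-dummy arm and potentially many from the two arms with active light. Both co-primary comparisons set an active-light arm against the corticosteroid-plus-dummy arm, so a safety contrast along the same lines would leave out low-grade light reactions on one side only. A reader given only that proportion could not tell how much low-grade erythema accompanied light treatment at home.

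The timing adds a second, smaller problem. If the definition changed while participants were already on treatment, the recorded events may mix two definitions.

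**Working it through.** The document states no erythema rate, no expected adverse-reaction rate and no power for safety, so there is no figure to reproduce. The check is a comparison of sections, followed by an illustration.

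**1. Does the exception reach the endpoint?** The exception is worded in terms of adverse events, the endpoint in terms of adverse reactions and device effects. Adverse reactions are ordinarily a subset of adverse events, so what is not an event is not counted as a reaction either. Table 3, however, describes grades 1 and 2 as expected reactions. The natural reading is that they are excluded, but the article does not say so outright; hence *apparently*.

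**2. Is there a conflict?**

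| Section | Grades 1–2 | Grades 3–4 |
|---|---|---|
| Light therapy: NB-UVB device | adverse reaction (no grade limit) | adverse reaction |
| Safety outcomes | not an adverse event | not exempted |

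The two rows disagree on grades 1–2 only. Blistering, burns, pruritus and the other listed light reactions are not exempted.

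**3. Which arms are affected?** Light therapy: dummy device says that the dummy has no known side effects and that it blocks the UVB. The exception therefore acts mainly on light-only and on combination therapy.

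**4. Size.** For one arm, let *C* be the proportion with any reaction that still counts and *r* the proportion with at least one episode of grade 1–2 erythema. With these episodes included, the proportion lies between max(*C*, *r*) and *C* + *r* (at most 1), depending on overlap. The endpoint thus rises by at most *r*. The document gives neither *C* nor *r*.

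As an illustration only, with 516 / 3 = 172 per arm (Sample size) and 2 × 172 = 344 in the two light arms:

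| Assumed *r* in light arms | 344 × *r* |
|---|---|
| 10% | 34 |
| 30% | 103 |
| 50% | 172 |
| 70% | 241 |

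Each figure is the most participants that could be left out at that rate; anyone with another counted reaction is already in the numerator. The rates are assumptions. The table shows that the answer depends entirely on a quantity that the article does not supply.

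**5. Timing.** The first randomisation (July 2015) precedes version 3.0 (30 September 2015) by about two to three months. The article gives neither the number randomised in that interval nor the date on which sites adopted the new rule, so the number affected is unknown.

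**The case against.** The rule is explicit, comes with a reason and is disclosed in the amendment table. Absence of erythema is the trial's own signal for raising the dose (Table 2, question 3), which makes it reasonable to see mild redness as part of the treatment. Leaving it out of a composite proportion also keeps it from swamping rarer and more serious reactions. All of this stands, and it is why the reporting exemption can remain. It does not remove the disagreement between the two sections, or the uneven effect on the arms.

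It can also be said that low-grade erythema could be described by arm under the full protocol or the analysis plan, neither of which is shown. That also stands: this point does not rest on a missing table. It rests on a definition that the article does state.

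Four stronger readings are tempting but not supported:

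- **Harm in the light arms is undercounted.** This follows only if grade 1–2 erythema is regarded as harm. What can be said is that low-grade *reactions* would be understated by the counted proportion alone.
- **Low-grade erythema is lost from the trial.** The article does not say that it goes unrecorded. Table 1 schedules adverse reactions at the two-week call, at the 3-, 6- and 9-month visits and in the diary.
- **It is the most frequent reaction, and Table 2 classes it as symptomatic.** No frequencies are given, and coming first in a list is not a rank. The word symptomatic in question 5 belongs to a published list of questions, not to the trial's grading.
- **Staff who had guessed the allocation decide what counts as a reaction.** The article does not say who attributes non-serious events. The guessing rates it quotes come from the earlier trial of active against dummy devices.

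**Conclusion.** The point holds as a matter of definition. Safety outcomes and the device section disagree on whether grade 1–2 erythema is an adverse reaction, and the endpoint apparently follows the narrower view. The consequence has a clear direction, namely fewer counted low-grade reactions in the two active-light arms with little effect in the dummy-light arm, but no size that the document can supply. The primary effectiveness analysis and the sample size are untouched.

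The conclusion rests on two assumptions: that an event not classed as adverse is also not counted as an adverse reaction, and that dummy-light participants have little such erythema, as the stated absence of known side effects suggests. A change of definition affecting early participants is a possibility raised by the dates, not something that the article shows to have happened in the data.

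**What to change.** 1. Reconcile Safety outcomes with the device section by stating which erythema grades count in the safety endpoint.
2. Apply that one definition to all participants, including those randomised before version 3.0, and say how their earlier records were handled.
3. Keep the exemption of grades 1 and 2 from adverse event reporting.
4. Beside the safety endpoint, tabulate the proportion of participants with erythema by grade and randomised arm, from the diary and visit data already scheduled in Table 1.

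The cost is a sentence or two of text and one descriptive table, with no change to treatment or to the visit schedule. The downside is that low-grade data may be incomplete, since the diary serves mainly as a memory aid and participants had no duty to report these episodes as adverse events. It must first be confirmed that grade was recorded. If it was not, the report should say so and should describe the endpoint as excluding grade 1–2 erythema wherever the arms are compared on safety.
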